### **9.2. Withdrawal of Individual participants**

Participants may discontinue the intervention or withdraw from the study for the following reasons:

- At the request of the child's family
- If the investigator considers that a participant's health will be compromised due to adverse events or concomitant illness that develop after entering the study

If a participant withdraws from the study intervention or from further follow-up visits, this should be documented in the participant records and electronic Case Report Form (eCRF) including the reason for withdrawal, whether study data collected up to that point can be used and whether further follow-up can be conducted.

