## **11.2. Phase 2**

Following screening, participants who score in the top 20% of population norms will be contacted by a member of the research team to see if they would like to participate in the full study.. For those that are selected, they will be contacted by phone and a date will be arranged for a member of the research team to visit them at home to complete the first assessment visit. At this stage it will be ascertained whether there are two parents in the family and whether both would like to take part.

This first assessment visit will take approximately 90 minutes with each family. During this visit the research team will provide additional written and verbal information about the study, and will allow participants to ask any questions about the study. The purpose of the study will be explained, as well as the procedures participants will be asked to complete. Participants will be informed that they can withdraw from any aspect of the home visits, and from the overall study at any time. The randomisation process will also be explained, so participants are aware that they will be randomly allocated to one of the two groups.

521 **11.3. Blinding**

522 Researchers assessing study outcomes will be blinded to randomised allocation. Participants (i.e. parents and their  
523 children) will be informed of their randomised allocation. In the event of a severe adverse event the Chief Investigator  
524 will be notified and may be informed of the randomised allocation.

525 **11.4. Randomisation**

526 Randomisation lists (one per site) will be prepared by a statistician using 1:1 allocation (ViPP intervention vs treatment  
527 as usual) and appropriate block sizes and uploaded on to InForm (the study electronic data capture system) prior to the  
528 start of the study. Eligible subjects will be allocated online to the next available treatment code in the appropriate  
529 randomisation list.

530 Randomisation will be stratified by treatment centre and by willingness and availability of both parents to be involved  
531 (versus one only).

532

533 **11.5. Follow-up visits**

534 Follow-up assessments will be undertaken in the family home by research assistants who are blind to treatment  
535 allocation, at a time convenient for the family.

536 Participants will be contacted by the research team prior to the visit time or the first post-treatment assessment and they  

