### 1502 3.6 Sample Size

1503 The total sample size will be 300 participants.

1504 If losses to follow-up are 20%, this leaves 120 participants per group with follow-up data. We would then have  
1505 80% and 90% power to detect standardised effect sizes of 0.36 and 0.42 respectively, at the 5% significance  
1506 level, using an independent samples t-test. In addition, we have stated that our analysis will adjust for baseline  
1507 behavioural score, research centre and age of child, and parental involvement (one versus two) which will  
1508 increase power, probably to over 90% for the 0.36 effect size (since such adjustment will reduce the residual  
1509 error variance in our model). Kahan and colleagues (2014, ref 1) found that covariate adjustment for 1 to 4  
1510 variables in trials increased power from 80% to a median of 93% power in their sample of 12 outcomes assessed  
1511 across 8 studies.)

1512 We have conservatively allowed for a potential drop-out rate of 20% because of the longer follow-up time in the  
1513 proposed study, even though previous intervention studies detailed below have maintained retention rates of  
1514 over 90% at follow-up.

1515 The pooled effect size for all randomised controlled trials to date that have used the same video feedback  
1516 intervention (ViPP) is 0.46 ([name], 2013, personal correspondence). Other relevant literature  
1517 for interventions for behavioural problems, predominantly in slightly older children, yield higher effect size  
1518 estimates. In the systematic reviews undertaken for the most recent NICE guidance on conduct disorders in  
1519 children and young people (ref 2), the pooled effects for parent-focussed interventions yielded estimated effect  
1520 sizes of 0.69 standard deviations for researcher-rated outcome (the main outcome measure in the proposed  
1521 study), and 0.54 for parent-rated outcome. In a study of the Incredible Years programme in 2-9 year olds (ref 3)  
1522 effect sizes ranged from 0.48-0.78. In the SPOKES trial (ref 4) of intervention for parents of 6 year olds, the  
1523 effect size for behavioural outcomes was 0.52 SD difference between the treatment and control group. Where  
1524 parenting programmes have been rolled out across the UK (ref 5-6) similar effect sizes have been found, albeit  
1525 in non-randomised designs (effect sizes ranged from 0.44-0.71).

1526

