| Informed consent                                                     | X |                                             |                                              |
| Inclusion & exclusion criteria                                       | X |                                             |                                              |
| Demographics and medical history                                     | X |                                             |                                              |
| AUDIT-C                                                              | X | X                                           |                                              |
| Randomisation                                                        | X |                                             |                                              |
| CBCL on child assessed by -
parent/care-giver 1                   | X | X                                           | X                                            |
| CBCL on child assessed by -
parent/care-giver 2                   | X | X                                           | X                                            |
| SDQ on child assessed by -
parent/care-giver 1                    | X | X                                           | X                                            |
| SDQ on child assessed by -
parent/care-giver 2                    | X | X                                           | X                                            |
| SDQ on child – assessed by teacher/
care-giver outside the family |   |                                             | X                                            |
| GAD-7 - parent/care-giver 1                                          | X | X                                           | X                                            |
| GAD-7 - parent/care-giver 2                                          | X | X                                           | X                                            |
| PPACS interview on child                                             | X | X                                           | X                                            |
| PHQ-9 – parent/care-giver 1                                          | X | X                                           | X                                            |

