### 3.10 Randomisation

Randomisation lists were prepared by a statistician independent of the trial ([name]) using computer generated 1:1 allocation (ViPP intervention vs treatment as usual) and variable block sizes. Randomisation will be stratified by treatment centre and by number of parents/ care-givers participating (one or two). The randomisation lists (one for each strata) will be uploaded on to InForm (the study electronic data capture system) and eligible subjects allocated online to the next available treatment code in the appropriate randomisation list.

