## 6.2 Primary Efficacy Analysis

The primary endpoint, externalizing behaviour (PPACS), will be analysed at follow-up, using the regression model suggested above, with multiple imputation of individual missing questions within the PPACS questionnaire, as described under treatment of missing values. This approach will maximise the power, by including baseline scores into the regression analysis. It will also ensure the most appropriate and unbiased treatment of anyone who has missing data on any item within the PPACS questionnaire. The primary analysis will also incorporate multiple imputation for anyone whose PPACS at outcome is completely missing (or with fewer items completed than the threshold). At 5 months follow-up, these will be imputed based on randomised group, gender of child, age of child at 5 month assessment, baseline PPACS, CBCL and SDQ scores. At 2 year follow-up, these will be imputed based on randomised group, gender of child, age of child at 2 year assessment, and PPACS, CBCL and SDQ scores (at 5 month follow-up, if available or else using these PPACS, CBCL and SDQ scores at baseline).

Sensitivity analyses will firstly be a complete case analysis (with multiple imputation solely of missing items within PPACS). We will perform further sensitivity analyses by assuming firstly that completely missing PPACS scores are one SDC lower (than anticipated by multiple imputation), and secondly by assuming that they are one SDC higher (than anticipated by multiple imputation) (truncated to maximum and minimum possible scores on PPACS). [SDC represents one standard deviation of changes in PPACS where changes are

calculated as PPACS at f/u minus PPACS at baseline]. There will be further sensitivity analysis, based on those with missing items within the PPACS questionnaire. They are filled in initially on a missing at random assumption, and then by assuming that they are one point higher on each item than MI prediction, and then one point lower (truncated to maximum and minimum possible scores on each item).

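### SAP 6.2 imputes a missing PPACS without the same-visit CBCL and SDQ (and, at 5 months, without the 24-month PPACS), so information already collected on the primary outcome can go unused

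*Combined protocol and SAP*

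**What the plan says.** SAP 6.2 makes multiple imputation of a completely missing PPACS part of the primary analysis. SAP 6.1 sets the threshold: a follow-up PPACS with fewer than 50% of its questions answered is treated in the same way.

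- **5 months.** The predictors are randomised group, gender of child, "age of child at 5 month assessment, baseline PPACS, CBCL and SDQ scores".
- **24 months.** The predictors are randomised group, gender, age at that assessment, and the 5-month PPACS, CBCL and SDQ, or the baseline scores if there are no 5-month ones.

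SAP 5.2 and the assessment schedule in SAP 3.9 place the CBCL and SDQ at both follow-ups, from the primary and, where possible, the secondary care-giver. At 24 months the schedule adds a further report, "SDQ on child – assessed by teacher" or another carer outside the family.

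On partial participation, protocol 11.2 tells parents that they "can withdraw from any aspect of the home visits". Protocol 9.2 begins "If a participant withdraws from the study intervention or from further follow-up visits" and asks staff to record whether further follow-up is still possible. SAP Table 9.3 has rows for 5-month CBCL and SDQ under a column for children whose PPACS is missing at 5 months.

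**The concern.** Imputation rests on the missing PPACS being predictable, without systematic error, from the variables in the model. That is hardest to believe when loss is related to how the child is behaving at the time. Baseline scores, taken five months or more earlier, carry limited information on that. Care-giver reports from the same visit carry more, and the 24-month PPACS carries some information about the 5-month value.

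Leaving these out means that a ViPP family with no usable interview but a poor same-visit CBCL is imputed as a typical ViPP family with the same baseline scores. Participants know their allocation (protocol 11.3), so loss that differs by arm is conceivable. If that happens, the estimated treatment difference shifts. If it does not, the cost is some precision.

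**Working it through.** **1. The plan's own figure.** Inputs from SAP 3.6 and 3.10: "The total sample size will be 300 participants", "computer generated 1:1 allocation", and "If losses to follow-up are 20%, this leaves 120 participants per group with follow-up data". The stated result is "80% and 90% power to detect standardised effect sizes of 0.36 and 0.42 respectively, at the 5% significance" level. Taking the test as two-sided (the SAP does not say), power is approximately Φ(d√(n/2) − 1.96) with n = 120:
- d = 0.36: 0.36 × √60 = 2.79; 2.79 − 1.96 = 0.83; power 79.6% (exact t: 79.3%).
- d = 0.42: 0.42 × √60 = 3.25; 3.25 − 1.96 = 1.29; power 90.2% (exact t: 90.0%).

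The power statement reproduces. It is used here only for the effect size (0.36) and the loss rate (20%, or 30 of 150 families per arm).

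**2. Assumptions not in the documents.** PPACS correlates 0.5 with its baseline value and 0.65 with the same-visit CBCL. About 20% of PPACS are missing. In ViPP only, loss rises by 0.8 in log-odds per SD of current questionnaire-reported behaviour. The true effect is 0.36 SD. Missing values are filled by regression imputation, which is the point estimate that multiple imputation approaches with many imputations.

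**3. Large-sample results, loss driven by the questionnaire score in ViPP only.**

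| Imputation model | Estimated effect (true 0.36) |
|---|---|
| Planned, including baseline CBCL | about 0.42 |
| Plus same-visit score, 25% questionnaire return | about 0.40 |
| Plus same-visit score, 50% return | about 0.39 |
| Plus same-visit score, 100% return | about 0.36 |

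The bias is 0.42 − 0.36 = 0.06 SD. With 20% missing in that arm, this equals an unmodelled gap of 0.06 / 0.20 = 0.30 SD between the ViPP families without a PPACS and their imputed values. What remains is roughly 0.06 × (1 − return): 0.045 at 25%, 0.03 at 50%, 0 at 100%. If baseline CBCL is left out of the planned model, the estimate is about 0.43 to 0.44, but the SAP does include it.

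Other inputs: with 10% missing the planned model gives about 0.39; with a same-visit correlation of 0.4 or 0.8 it gives about 0.39 or 0.44. With full return, the added scores bring each back to about 0.36.

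**4. Other loss mechanisms.**
- *Loss depends on PPACS itself, ViPP only:* planned about 0.475, with same-visit scores at 100% return about 0.44. The bias falls from 0.115 to 0.08, so about 0.035 / 0.115 = 30% is removed.
- *Loss depends on behaviour in the same way in both arms:* 0.36 with or without the extra scores, so no bias.
- *Loss depends on behaviour in opposite directions in the two arms* (deliberately adverse; 150 per arm, 1,500 runs per setting, baseline correlation 0.5 to 0.7, same-visit correlation 0.4 to 0.8): planned 0.42 to 0.54, a bias of 0.06 to 0.17 SD. The added scores remove about 25%, 50% or 100% of it at those return rates.
- *Missing completely at random* (same settings): no bias. The standard error falls by about 0 to 6.5% (for example 0.1121 to 0.1049, or 6.4%) and power rises by about 0 to 3.5 points.
- *Questionnaires always missing with the PPACS:* same-visit scores add nothing.

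**5. Do the planned sensitivity analyses cover this?** The complete-case analysis brings in no further data. The shift of one SDC up or down is not described as differing by arm. Applied in one direction to both arms with 20% missing in each, it moves each mean by 0.20 SDC and the difference by zero. With 22% and 20% missing, it moves the difference by only 0.02 SDC.

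**The case against.** The strongest reply is that the affected group may be very small. All three instruments are scheduled at the same visits, and SAP 3.6 treats the 20% as families without follow-up data, not families lacking only an interview. A family that misses the visit has no same-visit parent report to use. This stands: the benefit depends on a number that the documents do not give.

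A reader might infer from protocol 11.2 that parents will refuse the PPACS interview and still complete the questionnaires. The documents do not say so. The right to withdraw is general, and protocol 9.2 does not separate interview from questionnaire. Table 9.3 shows only that the combination is possible; the 50% completeness rule is another way it can arise.

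A reader might also infer that the planned analysis will overstate the effect. That needs loss that differs by arm in how it relates to behaviour, and nothing in the documents shows it. The full recovery in the main scenario is also built in, because loss there is driven by the very score that is added; when PPACS itself drives loss, recovery is partial.

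Protocol 13.2 does mention best-case and worst-case values in different randomisation groups. Such analyses probe non-random loss, but the SAP describes the SDC shifts without stating that they differ by arm, and neither approach uses the collected scores.

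Two limits on scope also stand. The point about a later PPACS applies only to the 5-month imputation, since the 24-month model already uses 5-month scores. And the documents do not state that the teacher SDQ can be obtained without a home visit.

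**Conclusion.** The point holds as a low-cost improvement to the imputation model. SAP 6.2 leaves out same-visit CBCL and SDQ at both follow-ups and the 24-month PPACS at 5 months, and no other section adds them. The consequence ranges from nothing (scores always missing together), through a modest gain in precision (standard error about 0 to 6.5% smaller), to removal of some or all of a bias of about 0.06 SD on a true 0.36 if loss follows current reported behaviour in ViPP only. Every bias figure rests on assumed correlations, about 20% missing and an arm-dependent mechanism; none is a prediction for this trial. Optional to moderate priority.

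**What to change.** In SAP 6.2, add to the imputation model for a missing PPACS:

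- the primary care-giver's CBCL and SDQ total scores from the same visit, at 5 and at 24 months;
- for the 5-month imputation, the 24-month PPACS total where available.

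Where these added scores are themselves missing, impute them in the same chained equations. Add secondary care-giver scores and the 24-month teacher SDQ only if the model still converges. Leave the regression model for the treatment effect unchanged. Report, by arm, how many families have same-visit questionnaires but no usable PPACS, so that readers can see how much the change could matter.

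The cost is SAP wording and a larger imputation model; no new data are needed. SAP 6.1 already warns that these models can be hard to fit, which is why the extra care-giver and teacher scores are conditional. Using the 24-month PPACS requires the 5-month analysis to be run once those data are in. Recruitment ended in July 2017, follow-up lasts two years, SAP version 2.0 is dated May 2019 and no interim analysis is planned, so this should be feasible if both time points are analysed together at the end.

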769 using scatter plots and box-plots. Continuous variables that follow an approximately Normal distribution will be

770 summarised using the mean and standard deviations. Skewed variables will be summarised using the median

771 and inter-quartile range. Categorical variables (binary and ordinal and multinomial) will be presented in terms of

772 frequencies and percentages.

773 Before starting the data analysis, the level, pattern and likely causes of the missingness in the baseline variables

774 and outcomes will be investigated by forming appropriate tables. This information will be used to determine

whether the level and type of missing data has the potential to introduce bias into the analysis results or reduce substantially the precision of estimates for the proposed statistical methods. The primary outcome, externalizing behaviour (Pre-PACS), will be analysed at follow-up using linear regression analysis (after checking regression assumptions), adjusting for treatment centre, parental willingness to participate (one or two parents), for infant's baseline behaviour and for infant's age at randomisation. Sensitivity analyses will be undertaken, based on assuming that missing outcomes are the worst possible, or the best possible, in different randomisation groups. If these show that conclusions may differ based on missing values, then supplementary multiple imputation for missing values will be undertaken. These analyses will account for results of any losses to follow-up insofar as they pertain to differences in measured variables (i.e. under the assumption of missing at random). This will enable us to effectively incorporate information gleaned from earlier follow-up times when the final follow-up outcome is absent. This will be done by incorporating outcomes at earlier time points into the predictive model for the multiple imputation of the outcome at 2 year follow-up. Secondary outcome variables will be analysed similarly.

Categorical outcome variables will be presented by treatment group, and compared using logistic/ ordered logistic regression adjusted as per linear regression above.

A detailed statistical analysis plan will be prepared and signed off prior to any interim analyses.

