## 1990 10.2 Forest Plot for Sensitivity Analysis

1991 A forest plot will be plotted for PPACS primary outcome, firstly for our primary analysis, and then for specified  
1992 sensitivity analyses. For all analyses, missing items from within the PPACS questionnaire will be accounted for  
1993 by using a multiple imputation, as specified for the primary outcome analysis. Missing PPACS outcome data is  
1994 defined here as when PPACS is completely missing or sufficient items from within it are missing such that  
1995 multiple imputation is deemed inappropriate. These will be interpreted to determine whether or not it is possible  
1996 and/or plausible that missing data has biased the outcome findings. Similar sensitivity analyses may be  
1997 undertaken for SDQ and CBCL outcome total scores, this time averaging scores over primary and secondary  
1998 care-givers, prior to analysis, for those families where both are available. All PPACS sensitivity analyses will be  
1999 presented via such a Forest plot.

2000 All sensitivity analyses on PPACS listed in section 6.2 will be presented in these sensitivity forest plots.

2001

2002 **Change from official signed version of analysis plan:** This section now refers to the newly added sensitivity  
2003 analyses in section 6.2 on PPACS outcome and to the amended primary analysis.

2004 **Change from SAP version 1:** There is no-longer reference to average scores over primary and secondary care-  
2005 givers, since this does not feature in our main analyses. Hence it does not make sense to report these averages in  
2006 our sensitivity analyses.

2007

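### The SAP shifts wholly missing PPACS scores by the same one SDC regardless of arm, so with similar drop-out the check says almost nothing about missingness that differs by arm

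*Combined protocol and SAP*

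**What the plan says.** The primary analysis in SAP 6.2 uses multiple imputation for families whose PPACS is wholly missing or below the completion threshold. At 5 months "these will be imputed based on randomised group, gender of child, age of child at 5 month assessment, baseline PPACS, CBCL and SDQ scores". This is a missing-at-random (MAR) model with arm as a predictor.

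The sensitivity analyses in the same section start as follows: "Sensitivity analyses will firstly be a complete case analysis (with multiple imputation solely of missing items within PPACS"). Two shift analyses come next. The first assumes that "completely missing PPACS scores are one SDC lower (than anticipated by multiple imputation"); the second, that they are "one SDC higher (than anticipated by multiple imputation) (truncated to maximum and minimum possible scores on PPACS"). The unit is defined there: "SDC represents one standard deviation of changes in PPACS", where change is follow-up minus baseline. Neither run names an arm. The remaining analyses shift missing items by one point, leave out the adjustment for length of follow-up, or keep only interviews at least 80% complete.

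Protocol 13.2 describes a different check, "based on assuming that missing outcomes are the worst possible, or the best possible, in different randomisation groups", with multiple imputation as a supplement if that check showed that conclusions might change.

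SAP 10.2 states the use to be made of the sensitivity set: "These will be interpreted to determine whether or not it is possible" or plausible that missing data biased the findings.

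**The concern.** Missing outcomes bias a comparison of arms mainly when the families who leave differ from their MAR predictions in one arm and not in the other, or in opposite directions. That is a realistic possibility here. Parents know their allocation (protocol 11.3), and only the ViPP arm is asked to host six sessions (protocol 7.1), so reasons for leaving may differ by arm. The documents give no evidence that they do.

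A shift of the same size and direction in both arms does not represent that situation. If the missing shares are similar, the two rows on the forest plot will sit almost on top of the primary estimate by construction, and a reader following SAP 10.2 could take this as evidence of robustness. The check also matters more under the SAP than under the protocol, because imputation of wholly missing outcomes has become the primary analysis.

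**Working it through.** **Inputs from the documents.** 300 families, 1:1 allocation, 20% loss leaving 120 per group, and 80% and 90% power for effects of 0.36 and 0.42 SD at the 5% level by t-test (SAP 3.6, 3.10). Earlier studies kept over 90% at follow-up (SAP 3.6).

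**Assumptions.** Two-sided test. The baseline/follow-up correlation r of PPACS is not given; I use 0.3 to 0.7 with equal variances. Unequal losses below are illustrations. Truncation is ignored because the PPACS range is not stated.

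**Step 1, the plan's own figure.** With 120 per group, power is 0.796 for 0.36 SD and 0.902 for 0.42 SD (exact t-test 0.793 and 0.900). The stated 80% and 90% are reproduced, on equal loss in the two arms.

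**Step 2, size of SDC.** SDC = SD × √(2(1 − r)): 1.18 SD at r = 0.3, 1.00 SD at r = 0.5, 0.77 SD at r = 0.7.

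**Step 3, effect of a shift.** Let pV and pC be the missing shares and dV and dC the shifts. With covariates balanced by randomisation, the adjusted difference (ViPP minus control) changes by

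pV × dV − pC × dC.

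For a common shift d this is d × (pV − pC).

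**Step 4, equal loss.** Change in the effect:

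| Shift in ViPP, control | 20% loss per arm | 10% loss per arm |
|---|---|---|
| +1, +1 SDC (as planned) | 0.20 − 0.20 = 0.00 SDC | 0.10 − 0.10 = 0.00 SDC |
| +1 SDC, none | 0.20 SDC (0.15 to 0.24 SD) | 0.10 SDC (0.08 to 0.12 SD) |
| +1, −1 SDC | 0.20 + 0.20 = 0.40 SDC (0.31 to 0.47 SD) | 0.10 + 0.10 = 0.20 SDC (0.15 to 0.24 SD) |

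SD ranges run from r = 0.7 to r = 0.3.

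**Step 5, the planned common shift with unequal loss.**

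- 22% against 18%: 0.04 SDC (0.03 to 0.05 SD)
- 25% against 15%: 0.10 SDC (0.08 to 0.12 SD)
- 30% against 10%: 0.20 SDC (0.15 to 0.24 SD)

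**Step 6, simulation.** 2,000 trials per scenario, 150 per arm, r = 0.5, true effect −0.36 SD, baseline-adjusted regression, one imputation per trial with arm in the model. At 20% loss in both arms the mean estimate was −0.36 under MAR and −0.36 under both common shifts. It was −0.16 with ViPP alone shifted up and +0.04 with opposite shifts. At 25% against 15%, the common shifts gave −0.25 (up) and −0.46 (down), against −0.36 under MAR. These agree with the formula.

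**The case against.** A fair defence has several parts.

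- **Cancellation is conditional.** A reader might infer that the shifts always cancel, or that the plan cannot detect attrition bias at all. The documents do not support that. Exact cancellation needs equal missing shares and no truncation that acts differently by arm. Equal 20% is a planning figure, and no observed loss by arm is given. With unequal loss the planned runs do test a common departure from MAR. This stands, and it limits the point to similar drop-out and to departures that differ by arm.
- **The interval can move even if the estimate does not.** At r = 0.5 and 20% loss, a common shift adds about 0.2 × 0.8 × 1² = 0.16 to a residual variance of 0.75, so the standard error grows by √(0.91/0.75) ≈ 1.10. A borderline result could change. True, but that is added noise and not a test of differential missingness.
- **The loss may be smaller.** The SAP calls 20% conservative. At 10% the movements halve, as shown above. This stands.
- **Item-level shifts.** A reader might infer that the one-point item shifts share the defect to the same degree. The SAP attributes missing baseline items to questions that do not apply to younger children, and age is in the model. Nothing in the documents points to item missingness that depends on arm.
- **Deliberate withdrawal.** A reader might infer that the sponsor chose to abandon the protocol's check. The SAP does not say so, and the protocol scenarios served partly to trigger imputation that is now primary. What can be said is that the two documents differ. SAP 6.1 does footnote its departure on centre effects, but there is no such note here.

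None of this supplies an analysis with departures that differ by arm. The complete-case and 80%-complete analyses impose no departure from MAR on absent outcomes.

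**Conclusion.** The concern holds in a limited form, and the SAP should be changed. As written, and reading the absence of any named arm as a common shift, the analysis is close to uninformative about arm-differential missingness if drop-out is similar: the point estimate moves by 0.00 SDC at 20% loss in each arm. The untested departures could move it by 0.20 to 0.40 SDC at 20% loss (0.15 to 0.47 SD over r = 0.7 to 0.3), or 0.10 to 0.20 SDC at 10% loss, against a design effect of 0.36 SD. The SD figures rest on the assumed correlations; the SDC figures depend only on the missing shares and the absence of truncation.

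A reader might go further and conclude that the primary estimate is biased. Nothing here shows that. The primary model and its imputation are untouched; what is affected is how much reassurance the SAP 10.2 forest plot can give.

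**What to change.** In SAP 6.2 and 10.2, keep the two common shifts as extra rows and add:

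- ViPP missing scores shifted by one SDC, up and down, with control left at its MAR imputation
- control missing scores shifted by one SDC, up and down, with ViPP left at MAR
- shifts in opposite directions in the two arms, both ways round

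State in 6.2 which arm each shift applies to, and show the number of wholly missing PPACS scores by arm beside the plot. Reconcile 6.2 with protocol 13.2, either by noting that these rows replace the best/worst scenarios or by restoring those scenarios. A grid of shifts reporting the tipping point, and arm-specific item-level shifts, are optional.

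The cost is SAP wording and a few more forest-plot rows, with no new data. The result may look less robust than under the present plan.
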